## Abstract

**Background:**

The primary objective of this study is to investigate whether a novel prosthetic foot with a polycentric ankle, which offers side-to-side adaptability, improves mobility and daily performance in individuals with (1) unilateral above-knee amputation, (2) unilateral below-knee amputation with a lower mobility level (K2) , or (3) bilateral amputation, any level of amputation. Traditional prostheses are primarily designed for forward walking and lack adaptability for navigating uneven terrain, turning, and executing other multidirectional tasks, often resulting in pain, instability, and limited function.

**Objective:**

The objective of this testing protocol is to better understand the functional impact of a novel foot design that offers more inversion/eversion rotation of the polycentric ankle. Although the foot has the potential to address mobility challenges, it is unknown whether people with different amputations and mobility levels respond differently.

**Methods:**

The study includes community-based mobility assessments, standardized questionnaires, and participant feedback. Although side-to-side adaptability prosthetic feet have shown benefits for highly active users, this study aims to evaluate the impact on individuals with more significant mobility limitations.

**Results:**

Results may guide prosthetic prescription, expand access to advanced prosthetic technology, and inform reimbursement policies, particularly benefiting veterans and service members with combat-related amputations. The study began recruiting in October 2023; as of September 2025, there were 66 participants (17 below the knee, 34 above the knee, and 15 bilateral) who completed the protocol. The clinical trial is expected to be completed by March 2027. Dissemination of results is expected to be completed by December 2027.

**Conclusions:**

This procedural study presents a model for evaluating prosthetic feet and other mobility-assistive technologies in real-world contexts, supporting broader efforts to match components to user needs through clinical trials that are grounded in both functional performance and user experience.

## Introduction

According to 2005 projections, over 1 million adults in the United States live with lower extremity amputation (LEA) [1], with approximately 22,000 people undergoing above-knee amputations annually [2]. Additionally, about 12,000 individuals have bilateral amputations, though precise figures are unavailable [1]. The largest group of individuals seen by prosthetists consists of those with transtibial amputations and limited mobility, classified at Medicare Functional Classification Level (MFCL) K2, accounting for 36% of the lower extremity amputee population [3]. A person with LEA at MFCL K2 can use a prosthesis for transfers and ambulation on level surfaces, with the potential to walk in environments with low-level barriers such as curbs, stairs, or uneven surfaces.

Advancements in prosthetic technology have significantly improved the mobility and quality of life for individuals with LEAs. However, the challenge remains in providing tailored prosthetic solutions that optimize both functional outcomes and personal satisfaction for diverse patient populations, especially those with unique needs such as warfighters, veterans, and individuals with bilateral or above-knee amputations. The importance of patient-specific prescriptions cannot be overstated, as prosthetic components must meet the specific biomechanical requirements of each individual to maximize effectiveness.

The need for innovative solutions is particularly pressing for individuals with higher levels of amputation and those experiencing lower levels of mobility. For example, individuals with bilateral amputations face persistent difficulties with balance, cognitive focus during gait, overall mobility, and residual limb pain despite using conventional prosthetic devices. Recent developments in prosthetic ankle technology have shown promising improvements, particularly in enhancing the foot’s adaptability to different surfaces, which is crucial for optimizing function in various environments. The META Arc (WillowWood), shown in Figure 1, features 10 degrees of frontal plane motion, which may enhance mobility, balance, and function during activities that benefit from this additional motion, such as turning, side steps, and backward steps.

**Figure 1. F1:**
[figure not shown]
META Arc (WillowWood).

In our previous study, 21 participants with unilateral below-knee amputation had 16 models of usual prosthetic feet, making comparisons between the usual foot and an investigational foot challenging [4]. Also, comparisons with the usual foot do not isolate the benefits of the unique features of the investigational foot. In the previous study, a locking feature eliminated the mediolateral motion, rendering the foot comparable to a typical energy storage and return foot. This was only completed for gait testing protocols in the laboratory; participants stated they had no opportunity for community testing of the locked version. The current study attempts to overcome some of these limitations.

This paper outlines the procedural approach for a randomized clinical trial designed to evaluate the impact of a novel frontal plane ankle technology on individuals with above-knee or bilateral amputations or those with below-knee amputations classified at an MFCL K2. By using a double crossover design and focusing on person-centered outcomes, this study seeks to improve our understanding of how advanced prosthetic feet can enhance functional mobility, balance, and daily activity participation for individuals with complex amputation profiles. A two-period or double crossover research design provides more data per participant, balances potential carryover effects, and improves statistical power and precision by having each participant’s response with the usual prosthetic foot, with the novel foot in both the locked and unlocked position, and with the usual prosthetic again. The mixed methods approach used in this study, which incorporates qualitative insights from interviews, daily experiences recorded in logbooks, and surveys, along with objective measures from standard functional tests, provides a comprehensive evaluation of the novel prosthetic foot. This protocol paper can be a model for not only evaluating prosthetic components but other assistive technologies as well.

The findings from this ongoing study are expected to have far-reaching implications for clinical practice, particularly for military service members and veterans who often face unique and severe challenges related to limb loss. With more than 1 million individuals living with LEA in the United States, and a significant portion of these being veterans or military personnel, the outcomes of this research will provide valuable insights into how personalized prosthetic technology can improve long-term mobility and quality of life for this population. This study challenges prosthesis users to move sideways, move backwards, and turn. By completing well-studied clinical assessments on an instrumented walkway, this study allows for biomechanical component analysis, providing more insight into prosthesis use and design.

## Methods

### Overview

This prospective multisite randomized double crossover clinical trial study will follow an A1-B1-B2-A2 design that includes military veterans and civilians. Three collaborative sites will recruit and enroll participants: (1) University of Washington (Seattle, WA), (2) WillowWood (Mt. Sterling, OH), and (3) University of South Florida (Tampa, FL). Prior to data collection, the principal investigators and main study personnel from each site participated in a study protocol training session to ensure data collection at each site was the same. The study personnel meet every other week to discuss study procedures.

### Ethical Considerations

The study received approval (STUDY00017239) from the University of Washington’s institutional review board (IRB); the IRBs of the other sites and the US Army’s Office of Human Research Oversight reviewed the study protocol. The protocol is listed in the federal clinical trial registry (ClinicalTrials.gov NCT06214026).

All participants will provide informed consent. Study data will be confidential. There will be links between study data and participant identifiers that will be kept in separate secured areas. The link between participant identifiers and the research data will be destroyed after the records retention period required by state and/or federal law. All the information provided by the participants will be confidential.

After the completion of visits 2, 3, and 4, participants will be compensated US $200 per visit for a total of US $600. Parking, mileage, and transportation (within limits) will be paid for study visits.

### Participants

The study includes three groups of individuals with amputations: (1) people with a unilateral above-knee amputation, (2) people with bilateral LEAs, and (3) people with a unilateral below-knee amputation who are categorized as having a K2 limited community ambulation level of mobility. All participants must be able to provide written informed consent independently and have the ability to read, write, and comprehend English.

Past research studies of people with amputations have historically underrepresented specific groups. Barriers to participation in clinical trials have been identified. This study targets individuals in these categories, and accommodations have been made. These included flexible payment schedules for participation, free rideshare transportation organized by study staff, free parking for participants who had their own transportation, and an on-call prosthetist. In addition, the study enrollment period was 3 years, enabling participants to delay protocol initiation due to socket changes, skin issues, or personal factors.

### Eligibility Criteria

To be eligible for the study, participants must be 16 years or older and reside in an independent living environment within the community. They may use a walking aid but should not primarily rely on wheelchair mobility.

### Exclusion Criteria

The weight limit is 165.6 kg (365 lbs). Participants must not have conditions, such as skin wounds, that would preclude the use of a prosthesis. Young children will not be included because they have different functional needs compared to adults. People will be excluded if they have fluctuating conditions that may significantly alter gait mechanics during the 10-week study. Examples include Parkinson disease, alcoholism, brain tumors, and hereditary cerebellar ataxias.

### Discontinuation Criteria

Participants will be discontinued from the study if they are unable to use a prosthesis. Examples include surgery or trauma. However, due to the potential for fluctuations in prosthesis use among this population, short-term issues will not disqualify individuals from continued participation.

### Procedures

#### Randomization

Stratified by study site, block randomization will be used to determine the order in which participants receive the locked and unlocked investigational prosthesis. Randomization will be completed and maintained through Research Electronic Data Capture (REDCap), a secure, Health Insurance Portability and Accountability Act–compliant web application for building and managing online surveys and databases.

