#### Study Procedures

##### Overview

This study uses a randomized double crossover clinical trial to evaluate a carbon fiber prosthetic foot with a frontal plane–adaptable linkage in two configurations: (1) unlocked, allowing frontal plane motion, and (2) locked, restricting frontal plane motion. When locked, the foot functions comparably to a conventional energy-storing-and-returning carbon fiber foot. A secondary aim is to compare the unlocked configuration to the participant’s usual prosthetic foot, representing the current standard of care.

The study follows an A1-B1-B2-A2 crossover design:

A conditions involve the use of the participant’s usual prosthetic foot.B conditions involve the study foot with the linkage either locked or unlocked. The order of the B conditions is randomized using block randomization stratified by study site.

A custom-designed pin system is used to lock the linkage and prevent frontal plane motion when required.

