### Statistical Analysis

The primary analysis will compare the META Arc foot in locked versus unlocked configurations. Statisticians will remain blinded to condition labels, analyzing outcomes as Condition X versus Y, with knowledge of the order (X→Y or Y→X), but not which corresponds to locked or unlocked.

Descriptive statistics (means and SDs for continuous variables; counts and percentages for categorical variables) will be used to summarize participant characteristics, stratified by amputation group. All analyses will be performed separately for each group.

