### Primary Outcomes

Primary performance outcomes include the TUG, the 3XF8W, and the Four Square Step Test. Assumptions of normality and homogeneity will be tested. If met, a multivariate analysis of variance (MANOVA) will be used to evaluate the effect of foot configuration at α=.05. A permutational MANOVA will be used if assumptions are violated. If multivariate differences are significant, post hoc paired *t* tests (or Wilcoxon signed-rank tests if nonnormality is present) will be used to assess individual outcomes without correction for multiple comparisons. In order to help control the familywise type I error risk, pairwise comparisons of the primary outcomes will only occur if the multivariate difference comparison from the MANOVA is significant.

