### Power

With n=30 for the above-knee and K2 groups, the study is powered (>80%) to detect a standardized effect size of 0.53. In the bilateral group (n=16), the power is greater than 50% for the same effect size. Preliminary data show larger effects (eg, 0.98 for the 3XF8W), supporting adequate power. Although underpowered to detect a meaningful difference in the bilateral group, 16 subjects is in line with other gait studies that have published data on 10 [13], 15 [14], or 19 [15] subjects with bilateral amputations, a challenging population to recruit and enroll. The study is also powered (81%) to detect a 75% preference for one configuration (vs 50% under the null) using a sign test with n=30. Although no minimal clinically important difference has been established, it is predicted that a standardized effect of at least 0.50 will correspond to an impactful improvement in participants’ physical function.

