## Results

This study protocol, funded by the Department of Defense Orthotics and Prosthetics Outcome Program (OP220033), was approved by the University of Washington’s IRB, the University of South Florida’s IRB, and the US Army’s Office of Human Research Oversight in March of 2023. As of September 2025, a total of 66 subjects have completed the study, including 17 with below-the-knee prostheses, 34 with above-the-knee prostheses, and 15 bilateral prosthesis users. The recruitment and data collection period of the study is expected to be completed by March 2027. Dissemination of results is expected to be completed by December 2027.

It is expected that the side-by-side adaptability of the investigational prosthetic foot will improve community functions such as gait over uneven ground and cross slopes, weight shift during two-legged standing, side-stepping, turning, and precise positioning of the foot at initial stance. Evidence from this study is intended to help clinicians weigh options regarding the use of a prosthetic foot with a passive adaptable ankle in the frontal plane for their patients.

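### Order is balanced by site but analysed within amputation group, and the stated primary tests carry no period term to absorb the chance imbalance that can result

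*Protocol article*

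**What the plan says.** The Randomization section gives one stratification factor: "Stratified by study site, block randomization will be used to determine the order in which participants receive the locked and unlocked investigational prosthesis". The Study Procedures overview repeats it: "The order of the B conditions is randomized using block randomization stratified by study site". Block size is not given.

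The Statistical Analysis section makes amputation group the unit of every analysis: "All analyses will be performed separately for each group". Power is also stated by group: "With n=30 for the above-knee and K2 groups, the study is powered (>80%) to detect a standardized effect size of 0.53", and "In the bilateral group (n=16), the power is greater than 50% for the same effect size".

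For the primary outcomes, "If met, a multivariate analysis of variance (MANOVA) will be used to evaluate the effect of foot configuration at α=.05", with a permutational version if assumptions fail. Next, "If multivariate differences are significant, post hoc paired" t tests, or Wilcoxon signed-rank tests, are applied to each outcome. No period or sequence term is named. The Secondary Outcomes section mentions carryover, to be handled in sensitivity analyses. The limitations paragraph of the Discussion allows that adaptation to the foot may run on into the next period and bias the results.

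On progress to September 2025, Results reports completers "including 17 with below-the-knee prostheses, 34 with above-the-knee prostheses, and 15 bilateral prosthesis users".

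**The concern.** In a two-period comparison of locked and unlocked, a learning effect between periods cancels from the mean within-person difference only if the two orders are equally frequent in the set being analysed. Here balance is forced within site, and each site's blocks mix the three amputation groups. Order inside a group is therefore only loosely constrained.

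This would matter little if the analysis removed the period effect itself, but a plain paired test does not. With unequal orders, part of the period effect enters the configuration contrast. With equal orders, the contrast is clean but the period effect stays in the residual variance and costs power. The group of 16 is the most exposed, and the article already calls it underpowered.

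**Working it through.** **Inputs from the article.** Three sites; strata by site only; groups of 30, 30 and 16; target effect 0.53; α=.05.

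**Assumptions not in the article.** Two-sided tests; blocks of 2, 4 or 6; equal recruitment by site; groups arriving in random order; a period effect π of 0.25 to 0.5, in SDs of the within-person difference within an order.

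**1. The stated power.** For a two-sided paired t test with noncentrality 0.53√n, power is 80.1% at n=30 and 50.9% at n=16. Both stated figures reproduce.

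**2. Order imbalance within a group.** Simulated with site-only blocks, with a fair coin for comparison:

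| Split or worse | Site blocks | Fair coin | Blocks within site × group |
|---|---|---|---|
| 11:5, n=16 | about 16% | 21% | 0–0.4% |
| 18:12, n=30 | about 25% | 36% | at most 0.5% |
| 20:10, n=30 | about 4% | 10% | 0% |

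Site blocks help somewhat, and results hardly change with block size.

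**3. Shift of the unadjusted contrast, given the split.** Write each person's difference between configurations as D = τ + sπ + e, with s = +1 in one order, −1 in the other, and SD(e) = 1. The mean of D is then τ + π(n₁ − n₂)/n.

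- 11:5: π × 6/16 = 0.09 to 0.19 SD, which is 18% to 35% of 0.53. Conditional type I error is 5.8% to 7.5%.
- 18:12: π × 6/30 = 0.05 to 0.10 SD. Conditional type I error is 5.1% to 5.2%.
- 20:10: π × 10/30 = 0.08 to 0.17 SD. Conditional type I error is 6.5% to 9.9%.

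**4. Equal orders, period left out.** The mean is unshifted, but the sample variance of D rises from 1 to about 1 + π²n/(n − 1). Simulated power at 0.53:

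| | π = 0 | π = 0.25 | π = 0.5 |
|---|---|---|---|
| n=30 (15:15) | 80% | 78.2% | 72.6% |
| n=16 (8:8) | 51% | 48.6% | 41.4% |

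Type I error falls below 5% in these cases, to about 3% at π = 0.5, so the test becomes conservative.

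**5. Period fitted.** The estimate is the average of the two order means of D. Its variance is ¼(1/n₁ + 1/n₂), its efficiency relative to equal orders is 4n₁n₂/n², and there are n − 2 degrees of freedom. The result does not depend on π.

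| Split | Efficiency | Power at 0.53 |
|---|---|---|
| 15:15 | 100% | 80.0% |
| 18:12 | 96% | 78.4% |
| 20:10 | 89% | 75.2% |
| 8:8 | 100% | 50.6% |
| 11:5 | 86% | 44.8% |

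Averaged over the splits that site-only blocks produce, period-adjusted power is about 79.2% (n=30) and 48.5% (n=16).

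**The case against.** The strongest reply is that order is randomised, so the unadjusted contrast is unbiased over randomisations. That stands. With π = 0.5 and coin-toss order, the unconditional type I error of the paired t test is 5.0% at both sample sizes. The shifts in step 3 apply only after an unlucky split.

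The size of the period effect is also an assumption. The Discussion raises the possibility without a figure, and at 0.25 SD the shift is half that at 0.5 SD. If there is no period effect, adjusting slightly lowers power. At 0.25 SD the effect on average power is small either way, and the gain is mainly protection against a shifted estimate. At 0.5 SD adjustment also gains power clearly.

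A full analysis plan might fit period. But the article states its primary tests explicitly, and those tests have no such term. Assessing carryover does not fill the gap, because carryover is distinct from a period effect.

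Changing the strata now would do little. The above-knee group has 34 completers against 30 planned, and the bilateral group 15 against 16. This stands and decides which fix comes first.

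A reader might infer that order within a group is no better than coin tossing, or that the trial is biased. The article supports neither: site blocks lower the tail probabilities (step 2), and the imbalance is random in direction.

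**Conclusion.** The mismatch is real and moderate in size. Allocation balances order on site, the analysis sets are amputation groups, and the stated primary tests do not remove a period effect that the article itself thinks possible. The risk is chance imbalance, largest in the bilateral group (11:5 or worse in about 16% of trials) and modest in the groups of 30 (20:10 or worse in about 4%). Separately from imbalance, omitting period wastes power whenever a period effect exists: about 2 to 7 percentage points at n=30 and 2 to 10 at n=16 over the assumed range.

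The probabilities rest on equal sites and random arrival of the groups. If one site recruited mostly one group, site blocks would balance that group better. The shifts and power losses rest on the assumed 0.25 to 0.5 SD. The stated power figures are not in error for a paired test without a period effect.

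**What to change.** **Main change.** State that the primary analysis of each amputation group includes period. Equivalently, take each person's period 1 minus period 2 differences and compare them between the two orders: a two-sample multivariate test (or its permutational version) for the joint hypothesis, then two-sample t or rank-sum tests for single outcomes. Report the realised order split in each group. The Statistical Analysis section already gives the statisticians the order under X and Y labels, so blinding is kept and nobody else is needed to count the split. This covers all three groups, including participants who have finished.

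**Cost.** One degree of freedom, and some power when the split is uneven: 51% to 45% at 11:5, and 80% to 78% at 18:12. The change should be fixed before condition labels are revealed.

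**Optional.** Add amputation group to the strata, with short blocks, for participants not yet randomised. This needs a new REDCap allocation table and a short amendment. The gain is limited and falls mainly in the K2 group, where 30 − 17 = 13 completers were outstanding in September 2025, some of whom may already have been randomised.
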